### Recruitment {15}

We will use consecutive enrollment of patients at two large study sites to help achieving adequate participant enrolment over an estimated period of 1 year. However, we can prolong the inclusion period if necessary. We will use roll-ups and flyers for awareness of the study towards the patients at each site.

## Assignment of interventions: allocation

### Sequence generation {16a}

We will use a 1:1 computer-based randomization module embedded in RedCap provided by OPEN using computer-generated random numbers and in blocks of four.

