#### Exclusion criteria

A language barrier that prohibits the exercise instructors/supervisors to provide sufficient or safe instructions during the intervention or at the general health lessonA known heart condition that prevents patients from actively participating safely in the exercise interventionKnown pregnancy, planned pregnancy, or pregnancy during the intervention period because pregnancy needs extra precautions in the pharmacological treatment, and exercise with high intensity is not recommended limiting these patients to participate in the exercise interventionDisabling musculoskeletal injuries that limit patients from actively participating in the exercise interventionSevere disease activity manifested clinically and with the need for urgent change in medical or surgical treatment strategy evaluated by the responsible physician

The responsible physician at the respective department of gastroenterology screens through the medical records for eligible patients. The screening information is not passed on to the research project, except for the personal identifier of patients and telephone number which are passed on to the research nurse. The eligible patients are approached at their upcoming appointment with information and the possibility to participate in the trial by the physician or research nurse. This is coordinated with the research nurse to ensure only eligible patients are approached at their forthcoming appointment. At each outpatient clinic, written information and posters will be used to inform patients of the trial and create awareness for the patients on the possibility to enter the trial.

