### Who will take informed consent? {26a}

We will use a consecutive inclusion of patients who fulfill the defined inclusion criteria. We plan with a recruitment period of 1–2 years. Patients will receive oral and written information on the current research project from the specialized health personnel, either physician or research nurse, in a quiet setting. After information, the patients are given at least 1 day of the consideration time, to determine whether or not they would be interested in participating and then give informed consent. If the patient wishes to have a relative present when receiving the information, this is encouraged and will be arranged at the study site. A research coordinator (nurse) will contact the patient who has accepted to be contacted after 1–3 days by telephone to confirm the acceptance of participation in the project. The patient will hereafter be asked to return a signed written pre-filled consent form.

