### Concealment mechanism {16b}

The research nurses do not have any access to the random list for the allocation of patients, because the list is incorporated in the randomization module and only a randomization button will appear in the system.

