### Implementation {16c}

The research nurse will generate the randomization at inclusion and according to the randomization, patients will be assigned to either the intervention arm or the comparison arm.

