### Methods for additional analyses (e.g., subgroup analyses) {20b}

We will perform adjusted and stratified analyses including mixed-effect models to examine other plausible differences, for example, differences in average causal treatment effect between men and women, and adjusting for site. We plan to explore differences in stratified analyses based on the patient type of disease, disease severity at baseline, type of pharmacological treatment at baseline, and physical activity level measured by accelerometry at baseline.

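### One fixed block size of four in an open-label trial, with the research nurse randomising, leaves allocation open to inference; how open depends on list details that the article does not give

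*Protocol article*

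**What the plan says.** Sequence generation {16a} sets equal allocation to the two arms through a module in the trial's REDCap database, "using computer-generated random numbers and in blocks of four". Only one block size is named.

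Concealment mechanism {16b} gives a single safeguard: "The research nurses do not have any access to the random list for the allocation of patients". The list sits inside the module and the nurse only triggers the next assignment.

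Implementation {16c}: "The research nurse will generate the randomization at inclusion and according to the randomization, patients will be assigned" to one of the two arms.

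Nurses also appear earlier in the enrolment chain. The text under Exclusion criteria says that eligible patients are offered the "possibility to participate in the trial by the physician or research nurse". Section {26a} adds: "A research coordinator (nurse) will contact the patient who has accepted to be contacted after 1–3 days by telephone", to confirm participation. Section {17a} states that neither participants nor healthcare personnel are blinded.

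For the analysis, section {20a} compares the primary outcome between arms with a t-test or a Wilcoxon rank-sum test. Site adjustment and "stratified analyses based on the patient type of disease, disease severity at baseline" appear only among the additional analyses in {20b}.

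**The concern.** Concealment requires that the person who decides whether and when a patient enters cannot foresee the next arm. A hidden list is necessary for this but not sufficient. In an open-label trial each allocation is visible once made, and with a constant block size the end of every block is determined by what came before it. A nurse who both deals with candidates and triggers the assignment could, in principle, let the timing of an inclusion depend on the arm expected next.

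The consequence would be selection bias, which no later analysis reliably removes. The primary outcome is a self-completed quality-of-life questionnaire in an exercise trial, so a difference between arms in patients' motivation could pass for a treatment effect. The Discussion section itself expects some patients to be wary of entering because they might not be allocated to exercise.

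A lesser matter is that the primary comparison carries no covariates. A chance imbalance between arms in site or disease type would therefore go uncorrected in the main result.

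**Working it through.** The plan states no figure for predictability, so there is none to reproduce.

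**Inputs.** Block size 4 and ratio 1:1 ({16a}); total 150 patients ({14}); two sites ({9}, {15}); personnel unblinded ({17a}). Assumed, because the article does not say: whether staff know the block size, whether the list is shared or per site, and which allocations a nurse can see.

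**Case 1: block size known and every earlier allocation on the list seen.** The six possible blocks are AABB, ABAB, ABBA and their mirror images, which gives 6 × 4 = 24 positions.

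- Certain positions: two in AABB (third and fourth) and one each in ABAB and ABBA (fourth). Total 2 × (2 + 1 + 1) = 8, and 8/24 = 33.3%.
- Best guess (name the arm behind so far in the block), expected number correct over the six blocks: position 1, 6 × ½ = 3; position 2, 4; position 3, 2 certain + 4 × ½ = 4; position 4, 6. Total 17, and 17/24 = 70.8%.
- For 150 patients there are 37 full blocks plus two patients: 37 × 8/6 = 49.3 certain allocations expected. This is an average, not a maximum.

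**Case 2: one list shared by two sites, own-site allocations seen only.** Simulation of 150 patients, with the nurse naming the arm that is behind at that site:

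| Site split | Correct guesses, shared list | Correct guesses, separate site lists |
|---|---|---|
| 50:50 | 52.9% | 70.6% |
| 70:30 | 53.7% | 70.6% |

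The site splits are assumptions. The guessing rule is a simple one, so the shared-list figures are a guide and not a proven ceiling.

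**Chance imbalance between arms within a site (same simulation).** Shared list: mean about 5 patients, 95th percentile 11–12. Separate site lists: mean under 1, 95th percentile 2.

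**Effect of varying the block size.** Simulation with a guesser who knows the set of sizes and all earlier allocations:

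| Block sizes | Certain in advance | Best guess correct |
|---|---|---|
| Fixed 4 | 32.9% (about 49 of 150) | 70.7% |
| Random 4/6 | 5.4% (about 8 of 150) | 69.3% |
| Random 4/6/8 | 2.3% (about 3 of 150) | 68.0% |

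The fixed-4 row is marginally below 33.3% and 70.8% because the last block is incomplete at 150. Varying the size removes most of the certainty but little of the average advantage.

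**The case against.** The strongest reply is that the large figures need conditions the documents do not establish. Nothing says that the recruiting nurses knew the block size. If one list served both hospitals and each nurse saw only local patients, guessing is little better than chance. Screening and approach are shared with physicians, the patient returns the signed consent form, and enrolment is meant to be consecutive, which works against holding a patient back. This all stands, and it is why the size can only be given as conditional. It does not remove the point. A block size of four can be inferred from the sequence, both sites enter data in one database ({18a}, {19}), and {5d} gives the whole research group access to the raw data. The article does not say whether recruiting nurses could see the other site's allocations.

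A reader might infer two stronger things, and neither is supported.

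- **That publishing the block size made allocations guessable.** The article is dated 20 November 2023, and Trial status gives 1 May 2023 as the extended end of inclusion. On those dates publication came too late to matter.
- **That the absence of stated strata is an error.** A condensed article may leave strata to the full protocol, unstratified randomisation is valid, and {20b} plans site adjustment and analyses by disease type. Stratifying by site would also make each list visible in full to its own nurse. Compared with a shared list seen only locally, it raises guessability from about 53–54% to about 71% with fixed blocks of four.

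**Conclusion.** The point holds in a conditional form. A single fixed block of four, unblinded staff and a nurse who may approach patients and also randomises mean that hiding the list does not by itself secure concealment. The exposure runs from about 53–54% correct guesses (shared list, own-site view, simple guessing rule) to 70.8% with one third of allocations certain (block size known or inferred, all earlier allocations on the list visible). The documents do not say where in that range the trial lies. Nor do they show that anyone predicted or steered an allocation, and the resulting bias in IBDQ cannot be calculated from them. Reading about 50 of 150 assignments as known to have been predictable would go beyond the evidence.

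This is a weakness worth correcting or disclosing. It does not invalidate the trial.

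**What to change.** 1. **For any patients still to be randomised:** load an allocation table with randomly varying block sizes, for example 4/6 or 4/6/8, not disclosed to recruiting staff. The cost is a new table from the database host and a slightly larger possible end-of-trial imbalance. An unfinished block of size b leaves the arms at most b/2 apart, so up to 3 (4/6) or 4 (4/6/8) patients per list instead of 2. If the list is stratified by site, note the trade-off: better balance within site, but each list more visible to its own nurse.
2. **In the primary IBDQ analysis:** include site and disease type as covariates, using a regression form of the comparison in place of the unadjusted t-test or rank-sum test. The cost is two prespecified terms. This deals with chance imbalance in those factors; it does not repair selection bias.
3. **If recruitment has closed, as the stated dates suggest:** report the fixed block size, whether the list was shared or per site, who knew the block size and who could see allocations, as a limitation on allocation concealment. The Discussion section currently mentions lack of blinding, and selection bias only as it affects generalisability. The cost is a few sentences.

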### Concealment mechanism {16b}

The research nurses do not have any access to the random list for the allocation of patients, because the list is incorporated in the randomization module and only a randomization button will appear in the system.

### Implementation {16c}

The research nurse will generate the randomization at inclusion and according to the randomization, patients will be assigned to either the intervention arm or the comparison arm.

## Assignment of interventions: blinding

### Who will be blinded {17a}

This study includes an exercise intervention that does not allow for the blinding of the participants or the healthcare personnel involved in the study.

### Procedure for unblinding if needed {17b}

No procedure for unblinding.

## Data collection and management

### Plans for assessment and collection of outcomes {18a}

We will create a research database hosted by OPEN in Odense, Denmark to enter and store the data, as this solution applies to the General Data Protection Regulation and Danish legislation to securely handle patient data. The research database is based on the system by Redcap and the database is available by any internet browser, allowing the sites to enter data directly into the database.

We will store the data for up to 5 years after the end of the project, and hereafter the data will be either transferred to the Danish National Archives and made anonymous, or destroyed.

Patients that are included in the study will have to have a blood sample (approximately 11.3 ml per patient) and a small fecal sample (approximately 2 × 3 ml per patient). The sample material and any excess material will be deposited in a research biobank after analyses during the project. The material in the research biobank will after the end of the project be stored for up to 5 years in a future biobank enabling any future research in relation to this project, and both biobanks follow the valid general data protection regulation. Patients also need to have external measures, such as waist circumference, blood pressure, and answer questionnaires regarding quality of life.

### Plans to promote participant retention and complete follow-up {18b}

The participating patients will be able to receive economical compensation for transportation expenses for the ambulatory visits. In case of withdrawal during follow-up in the intervention group, we will ask the patients whether they still could be interested in answering the electronic questionnaires or completing the ambulatory visits to ensure follow-up and likewise in the comparative group. However, the patients may at any time withdraw their consent to participate without any influence on their medical treatment.

### Data management {19}

The data entry is completed at the two sites by the research nurses and research physiotherapists using the electronic research database (RedCap). The database has incorporated range checks for numeric data, and the data will be checked by the principal investigator during the entire study period. The electronic surveys are directly sent to each patient’s e-box. All Danish citizens have an electronic e-box for communication with the state, and the e-box is linked to their civil registration number. The principal investigator manages access to the database. The accelerometers are sent in pre-paid envelopes from the participants to the principal investigator, where the data is loaded into a secured storage space hosted by OPEN. The database and storage use logging and follow the EU GDPR rules.

### Confidentiality {27}

All the personal information is stored in the research database during the study and up to 5 years after. Only the principal investigator and the research group have access to the data, and the data may not be used for any other purposes than described and approved by the regional ethics committee. The data must not be shared with others to protect the confidentiality of the participants, and data sharing will require new consent from the patients.

### Plans for collection, laboratory evaluation, and storage of biological specimens for genetic or molecular analysis in this trial/future use {33}

The blood samples and fecal samples are stored in a research biobank hosted by OPEN. The specimens are saved for 5 years in the biobank after the end of the study. All new studies that will use data must be approved by the local ethics committee, as well as the research group including the principal investigator.

## Statistical methods

### Statistical methods for primary and secondary outcomes {20a}

We will present descriptive statistics using absolute numbers and percentages. We will use the intention-to-treat (ITT) concept in our primary analysis of the specified outcomes on between-group differences from baseline to week 12. We will use parametric or non-parametric statistics for comparing the primary outcome in the interventional arm to the comparison arm. We use a *t*-test if the data is parametric and a Wilcoxon rank-sum test if the data is non-parametric to estimate the average causal effect of the intervention. We will use mixed model analyses with random effects to evaluate repeated outcome measurements at weeks 0, 4, 8, and 12, and to account for within-patient effects on our outcome measures opting for more precise estimates of treatment effects [43]. In a supportive analysis of the data, we will use a per-protocol (PP) strategy for handling protocol non-adherence. We will report the 95% confidence intervals for the average causal effects estimates. We will report our results according to the CONSORT statement for randomized clinical trials [44]. We will use STATA to process data and calculate the estimates.

### Interim analyses {21b}

There is no planned interim analysis, due to the short study period of 12 weeks. However, we will monitor any adverse events in relation to the intervention.

### Methods for additional analyses (e.g., subgroup analyses) {20b}

We will perform adjusted and stratified analyses including mixed-effect models to examine other plausible differences, for example, differences in average causal treatment effect between men and women, and adjusting for site. We plan to explore differences in stratified analyses based on the patient type of disease, disease severity at baseline, type of pharmacological treatment at baseline, and physical activity level measured by accelerometry at baseline.

### Methods in analysis to handle protocol non-adherence and any statistical methods to handle missing data {20c}

We will use a PP approach for handling non-adherence and examine the robustness of the ITT analysis results. In the PP analysis, we will include patients based on their adherence to the protocol considered as complete cases (e.g., patients with more than 80% show up in the intervention arm and complete follow-up in the comparison arm) and to analyze the specified outcomes on between-group differences from baseline to week 12 for this population. As specified earlier, we apply similar mixed model analyses in the PP approach as in the ITT. In supplement to the PP analyses and the possible non-adherence, we plan to use causal inference methods that include emulating data, for example, effects of different types of non-adherence or effects of concomitant treatment utilizing marginal structured models and inverted probability weighting to estimate the average treatment effect under these explorative additional questions [45, 46].

In the case of missing data in the ITT analysis, we will use multiple imputations with 10 imputations per missing value if the data is assumed to be missing at random or not missing at random. The multiple imputations will be based on regression models including predictive covariates and/or outcomes depending on which data are missing. We plan to use a linear model for continuous outcomes including covariates such as age, sex, type of disease, and disease activity. If data is assumed not to be missing at random, we will attempt to understand why and report the differences in our results by the complete-case approach and when imputation analyses are applied. To deal with any covariates or outcomes that are not normally distributed we will use log or other appropriate transformations [47]. We will perform sensitivity analysis with a best/worst approach to missing data as well as helping evaluate the robustness of the analysis.

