#### Sample size {14}

To calculate the number of patients needed in this trial, we have used a power of 80% and an alpha level of 5% (0.05) and used outcome differences observed in previous studies. We need to include at least 106 patients, with 53 patients in the intervention arm and 53 in the comparison arm to be able to detect a clinically relevant 13.8 (SD ± 25) mean difference in change between the groups on the IBDQ scale based on the similar changes observed in studies by Ng, Millard [12] and Klare, Nigg [9]. A minimum clinical important difference (MCID) for the IBDQ has previously been reported as an absolute change of 16 points in patients with Crohn’s disease; however, MCID for the IBDQ is not clearly defined [42]. We have performed a power analysis on the secondary and explorative outcomes, not reported, and overall we need to include a total of 100 patients in these analyses. Based on this, and to cover all outcomes including 33% drop-out, we have estimated a total study size of 150 patients, with 75 in both the intervention arm and the comparator arm.

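### Ten imputations are few for the drop-out the plan allows for: the primary result could depend on the random seed to an avoidable degree, although the analysis stays valid

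*Protocol article*

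**What the plan says.** Section {20a} makes ITT the basis of the primary analysis: the between-group difference from baseline to week 12. For missing data in that analysis, section {20c} states "we will use multiple imputations with 10 imputations per missing value", whether the data are taken to be missing at random or not. The imputation model for continuous outcomes is linear; age, sex, type of disease and disease activity are given as examples of covariates. The same section adds a complete-case comparison and a best/worst sensitivity analysis.

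The sample size section {14} states "We need to include at least 106 patients, with 53 patients in the intervention arm and 53 in the comparison arm", for a "clinically relevant 13.8 (SD ± 25) mean difference in change between the groups on the IBDQ scale". The total is then raised to 150 "to cover all outcomes including 33% drop-out". Under Explorative outcomes, quality of life is measured only at baseline and week 12, so no intermediate IBDQ value can inform the imputation.

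**The concern.** Multiple imputation is a simulation. With few imputations, the pooled estimate, its standard error and the p-value carry noise from the random draws, and this noise grows with the fraction of missing information. The protocol fixes the number of imputations at 10 and, separately, sizes the trial to withstand the loss of one third of its patients. If that loss occurred in the IBDQ, two analysts running the same plan on the same data could land on different sides of 0.05 when the result is near the threshold. The complete-case and best/worst analyses probe the missingness assumption and do not measure this noise.

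**Working it through.** **Inputs from the protocol.** 75 per arm, SD of change 25, design difference 13.8, power 80%, alpha 0.05, drop-out 33% (section {14}); 1:1 allocation (section {16a}); 10 imputations (section {20c}). Assumed: a two-sided test, which fits the 95% confidence intervals planned in {20a}; a t-test; values missing completely at random in each arm; treatment arm in the imputation model; R² of the covariates for IBDQ change between 0 and 0.5, since the protocol gives no figure.

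**The plan's own figure.** The normal approximation, 2 × (1.96 + 0.84)² × (25/13.8)², gives 52 per arm after rounding up. The exact t-test gives 53 per arm (power 0.804), so the stated 106 is reproduced.

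**Hand calculation, uninformative covariates.**
- Complete-data variance: 25² × 2/75 = 16.7 (SE 4.08).
- With one third missing, 50 per arm observed: 25² × 2/50 = 25 (SE 5.0).
- Between-imputation variance B ≈ 25 − 16.7 = 8.3; fraction of missing information ≈ 8.3/25 = 0.33.
- Seed-to-seed SD of the estimate = √(B/m): 0.91 points at m = 10, 0.50 at m = 33, 0.29 at m = 100.
- With R² = 0.3, B ≈ 8.3 × 0.7 = 5.8, and the SD at m = 10 is 0.76.
- A seed SD of 0.91 is 0.91/5.0 = 0.18 SE. Two such SDs move z = 1.96 to about 1.6 or 2.3, that is, p of about 0.11 or 0.02, before counting noise in the standard error.

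**Simulation.** Bayesian linear-regression imputation with arm and four covariates, pooled t-test, Rubin's rules with Barnard-Rubin degrees of freedom, two independent imputation runs per trial, 4,000 trials per setting. Share of trials with opposite verdicts at p < 0.05, for m = 10 and 33% missing:

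| True difference | R² 0 | R² 0.1 | R² 0.3 | R² 0.5 |
|---|---|---|---|---|
| 0 | 2.9% | 3.5% | 2.8% | 2.6% |
| 5 | 7.0% | 6.2% | 5.8% | 5.7% |
| 8 | 10.7% | 11.1% | 9.8% | 8.1% |
| 10 | 12.0% | 11.0% | 9.7% | 7.6% |
| 13.8 | 9.2% | 9.2% | 7.1% | 5.2% |
| 16 | 7.1% | 6.4% | 5.0% | 3.0% |
| 20 | 2.4% | 1.5% | 1.2% | 0.7% |

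The simulated seed SD is 0.78 to 0.94 points for R² up to 0.3, in line with the hand calculation. Rejection rates under no effect are 0.047 to 0.051.

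**Less missing data** (difference 13.8, R² 0.1, m = 10): 29% missing gives 7.6%, 25% gives 5.9%, 20% gives 4.9%, 10% gives 2.5%. With 20% missing and R² 0.3, the rate is 4.3%.

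**More imputations** (difference 13.8, R² 0.1, 33% missing):

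| m | Opposite verdicts | Seed SD (points) | Power |
|---|---|---|---|
| 10 | 8.7% | 0.88 | 0.760 |
| 33 | 4.6% | 0.50 | 0.772 |
| 50 | 3.9% | 0.40 | 0.779 |
| 100 | 2.4% | 0.29 | 0.783 |
| 200 | 1.6% | 0.20 | 0.789 |

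The two values at m = 10 (9.2% and 8.7%) come from separate runs; the simulation error is about √(0.09 × 0.91/4000) = 0.5 points. A further simulation, with imputation from arm and baseline IBDQ (correlation 0.5 to 0.6 assumed, 1,500 trials per setting), gave 7 to 8% at 13.8 and about 12% at 10 for m = 10. At m = 100 it gave 2 to 3% and 3 to 4%.

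**The case against.** **The 7 to 12% is conditional.** This stands. It needs a true difference of about 8 to 13.8, the full 33% missing and weak to moderate predictors. A reader might take it as a general property of the plan, which the tables above do not support.

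**The 33% is a drop-out allowance, not a forecast of missing IBDQ values.** This also stands. Section {18b} asks patients who withdraw, in either arm, whether they will still complete questionnaires, and these are sent electronically, so some values may be recovered. The required 106 of 150 would itself mean 29% missing. Still, 33% is the loss the plan chose to withstand, and the number of imputations should be adequate for it.

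**Better predictors shrink the noise.** True: at 13.8 the rate falls to about 5% when R² is 0.5. Section {20c} permits predictive covariates and outcomes in the model, but the protocol gives no basis for assuming so strong a prediction.

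**The inference remains valid.** This stands. Rubin's rules carry the finite number of imputations into the variance and degrees of freedom. A seed SD of 0.9 points is small beside an SE of 5, and verdicts change mainly where p is already near 0.05.

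**Seed choice.** A reader might infer that an open-label team could rerun the imputation until it liked the answer. Nothing in the protocol suggests this, and a pre-set seed, rather than more imputations, is what would guard against it. The seed and Monte Carlo error reporting are commonly left to the SAP, so their absence here is no fault. The point concerns only the number that the protocol does state.

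**Conclusion.** The point holds as a reproducibility improvement. Under the conditions named above, 10 imputations leave a seed SD of about 0.8 to 0.9 IBDQ points and opposite verdicts in about 7 to 12% of trials. The rate is about 3% under no effect, about 5% at a difference of 16, and about 4 to 5% at 13.8 with 20% missing. Type I error is not inflated, and power is about 0.76 at m = 10 against 0.78 at m = 100, a loss of about 2 points. It would be wrong to conclude that the planned analysis is invalid or that its interval is miscalibrated. The sizes rest on an assumed R², values missing completely at random, a t-test and treatment arm in the imputation model.

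**What to change.** In section {20c}, replace 10 imputations with a larger number: at least the percentage of incomplete cases (about 33 at the planned drop-out), and preferably 100 or more. Set the random seed in advance, in the protocol or the SAP. After the run, check the Monte Carlo error of the estimate and the p-value, and raise the number of imputations if that error could carry the p-value across 0.05. With 100 imputations, disagreement between seeds falls to about 2 to 4%; it is reduced, not eliminated. The cost is one changed number and minutes of computing time, with no effect on trial conduct.

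### Multiple imputation that is valid only under missing at random is also prescribed for data judged not missing at random, and the added complete-case comparison cannot reveal the resulting bias

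*Protocol article*

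**What the plan says.** Section {20c} of the protocol article sets one imputation rule for the intention-to-treat analysis: "multiple imputations with 10 imputations per missing value if the data is assumed to be missing at random or not missing at random". The models are regressions on predictive covariates, outcomes or both, depending on what is missing. For continuous outcomes the text adds: "We plan to use a linear model for continuous outcomes including covariates such as age, sex, type of disease, and disease activity".

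If the data are judged not missing at random, two further things happen. The investigators look for the reason, and they report how complete-case and imputed results differ. The section closes with "We will perform sensitivity analysis with a best/worst approach to missing data", without saying what value counts as best or worst.

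Four other sections bear on this:
- Sample size {14}: "to cover all outcomes including 33% drop-out, we have estimated a total study size of 150 patients".
- Criteria for discontinuing {11b}: participation stops if the physician considers an increase in disease activity significant.
- Retention {18b}: patients who withdraw are asked whether they would still complete questionnaires or visits.
- Outcomes {12}: quality of life is measured only at baseline and week 12.

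**The concern.** Regression imputation fills in a missing week-12 IBDQ as if the patient had behaved like observed patients with the same covariates. That is the missing-at-random assumption. Once the investigators have concluded that it fails, running the same imputation gives an estimate that rests on the assumption they have just rejected.

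Setting that estimate beside the complete-case result does not help. Under outcome-related drop-out both can be wrong in the same direction, so close agreement would reassure falsely.

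The risk is foreseeable here. The primary outcome is self-reported in an open-label trial, drop-out can follow from worsening disease, and no IBDQ is taken between baseline and week 12 to show how a patient was doing before leaving. At stake is whether the primary result stands if patients who did badly on exercise are the ones with missing questionnaires.

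**Working it through.** **Inputs from the document.** Difference 13.8 and SD 25; 80% power and alpha 5% (two-sided assumed); 106 patients before drop-out; 150 recruited, 75 per arm; 33% drop-out allowance (all {14}). Ten imputations ({20c}). t-test as the parametric primary test ({20a}).

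**The plan's own figure.** The normal approximation gives n = 2 × (1.96 + 0.84)² × 25² / 13.8² ≈ 51.5, so 52 per arm. The exact t-test gives 52.5, so 53 per arm and 106 in total, with power 80.4%. The stated "at least 106 patients, with 53 patients in the intervention arm and 53 in the comparison arm" is reproduced.

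**Bias when the data are not missing at random.** Let p be the fraction missing in an arm and k the number of points by which its drop-outs do worse than the imputation assumes. Then

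bias in the effect = p(exercise) × k(exercise) − p(comparator) × k(comparator).

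The document gives no k, so the values below are assumptions, with k(comparator) = 0.

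| k (exercise) | 10% missing | 20% missing | 33% missing |
|---|---|---|---|
| 5 | 0.5 | 1.0 | 1.7 |
| 10 | 1.0 | 2.0 | 3.3 |
| 20 | 2.0 | 4.0 | 6.6 |

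At 33% missing, k of 10 to 20 gives 3.3/13.8 = 24% to 6.6/13.8 = 48% of the design difference. The sign reverses if comparator drop-outs are the ones doing worse.

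**Does the complete-case comparison expose this?** A simulation used 1,500 trials, 75 per arm, 33% missing, ten imputations, and arm and baseline IBDQ both in the model. Its further assumptions are not in the document: baseline SD 30, slope of change on baseline −0.35, and drop-out in the exercise arm only correlated 0.7 with poor change.
- True difference 13.8: the imputed estimate is 21.8.
- No true difference: the imputed estimate is 8.0, and the test rejects in about 39% of trials.
- Complete cases, in closed form: the cut-off is z(0.67) = 0.44, with normal density 0.362. The bias is 25 × 0.7 × 0.362/0.67 = 9.5, giving 13.8 + 9.5 = 23.3.

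The two analyses differ by 23.3 − 21.8 = 1.5 points, while both are at least 8 points too high. This mechanism is harsher than the table: 8.0/0.33 corresponds to k of about 24. It shows what can happen and is not a forecast.

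**How wide might best/worst be?** Assume a shift of only 1 SD (25 points), in opposite directions in the two arms. The bounds are 13.8 ± 0.33 × (25 + 25) = 13.8 ± 16.5, or about −3 to 30. They include zero even when the design effect is true.

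**Why arm should be named.** If arm were left out of the model and values were missing completely at random, imputed patients would carry no treatment difference. The expected effect would be 13.8 × (1 − p): 12.4 at 10%, 11.0 at 20% and 9.2 at 33% missing. Simulated at 33%:
- without arm: about 9.3, power 44%
- with arm alone: 14.1, power 77%
- with arm and baseline IBDQ: 13.9, power 78%
- with baseline IBDQ alone: 9.2, power 45%

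Arm is therefore the variable that matters for bias.

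**The case against.** **The covariate list.** A reader might infer that the imputation model omits arm and baseline IBDQ, so that the plan itself leads to an estimate near 9.2 and power of 44%. The document does not support this. The list is introduced as examples, and the sentence before it admits any predictive covariates or outcomes. Both variables are unnamed, not excluded, and a full list commonly sits in an analysis plan that is not shown.

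**Absence of any check.** A reader might also infer that the plan has no check on departures from missing at random. It has one, the best/worst analysis, alongside the inquiry into reasons. What stands is that best and worst are undefined and that even a mild definition gives bounds that hardly discriminate.

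**The 33%.** This is a sample-size allowance, not a forecast of missing IBDQ. Patients who withdraw are asked to keep answering, and questionnaires go to them electronically ({18b}, {19}). The lower columns of the table may be the relevant ones.

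**Imputation as such.** Multiple imputation can be used for data not missing at random; the remedies below are forms of it. But it then needs a stated departure from the observed-data model, and {20c} states none.

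**Ten imputations.** This is a matter of precision, not bias. With a missing-information fraction of 0.33, Monte Carlo error is √(0.33/10) = 0.18 standard errors, which is not a flaw in the rule.

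**Conclusion.** The concern holds for the not-at-random clause. {20c} prescribes one method for two assumptions and it is valid under only one of them. The comparison offered as support shares the weakness. This is a stated rule, so an analysis plan could repair it only by departing from it.

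The size depends on two unknowns, the fraction missing and k. With 33% missing and an assumed k of 10 to 20 in the exercise arm alone, the effect is overstated by 3.3 to 6.6 points against 13.8. At 10% missing the same k gives 1 to 2 points. The direction is not fixed either, since comparator drop-outs doing worse would bias the effect downwards.

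Naming arm in the imputation model is a safeguard, not the correction of an error in the text.

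**What to change.** Reword {20c}, or settle it in the analysis plan before the data are analysed:

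1. **Missing at random.** Restrict standard multiple imputation to this analysis. Name randomised arm in the model, or impute within arm, and name baseline IBDQ. Site, disease type and the week 4 and 8 biomarkers are useful additions. Before listing week 4 and 8 disease scores, reconcile {12}, which says they are measured then, with the timeline in {13}, which shows them only at weeks 0 and 12.
2. **Not missing at random.** Replace the clause with a delta-adjusted tipping-point analysis that varies the shift separately by arm and reports where the conclusion changes, or with imputation of exercise drop-outs from the comparator arm, or both. If exercise drop-outs keep no benefit, this corresponds to k = 13.8, and the expected effect at 33% missing is 13.8 − 0.33 × 13.8 = 9.2.
3. **Best/worst.** Either define the values used or let the tipping-point analysis take its place.
4. **Optional.** Raise the number of imputations. Fifty would cut Monte Carlo error to √(0.33/50) = 0.08 standard errors.

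The cost is a few sentences and modest extra programming in Stata, with no new data.
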